### Interventions

Protocols for the two arms of the study will be described in a Standard Procedures Manual, available from the co-ordinating investigator. A guide for tailoring exercise prescription and advancement, as well as criteria for discontinuing allocated interventions, will be included within these protocols.

### Hospital inpatient rehabilitation

Those allocated to HI will be admitted to the adjacent rehabilitation hospital for 10 days. As per the private sector, HI participants will receive twice-daily supervised physiotherapy comprising 1 to 1.5 hour class-based exercises and 1 to 1.5 hour one-to-one therapy. Prior to discharge, participants will be familiarized with the home program as described below.

### Hybrid home program (standard care)

The HO will be based on what is standard care in the local health district, which is broadly based on the home program utilized in our most recent RCT [18]. The original home program was informed by guidelines for exercise in the elderly [20] and those with osteoarthritis [21]. Approximately 2 weeks post-surgery, participants allocated to the HO will attend one group-based outpatient exercise session in the physiotherapy department where the home program will be rehearsed and exercises individualized as required due to co-morbidities. The program comprises general aerobic components as well as general functional and muscle-specific exercises focused on restoring knee mobility, lower limb strength, and normal neuromuscular co-ordination and gait patterns.

Participants in both treatment arms will be encouraged to attend one to two classes from post-operative weeks 3 to 8 to encourage exercise progression and discuss any ongoing issues with the therapist. Participants will receive a booklet detailing the home program, and will be permitted to contact the therapist by phone in this period.

All participants will be required to complete a diary detailing program adherence, healthcare utilization, and social costs relating to carer-burden. Participant attendance at the outpatient classes will also be obtained from the treating physiotherapist.

### Outcome measures

The primary outcome and most secondary outcomes will be measured pre-operatively, at week 10 (the time when the home program formally ceases), and then at 6 and 12 months post-randomization (Table 2). Assessments will be performed by an observer blinded to the participants’ study allocation.

**Table 2 T2:** Outcome measures

**Primary outcome measure***	**Data collection instrument**
6 minute walk test*	6 minute walk test; physical test [19]
**Secondary outcome measures**	
Gait speed	15 m walk test; physical test
Knee injury and Osteoarthritis Outcome Score (KOOS)	KOOS [22]; patient-rated questionnaire
Oxford Knee Score (OKS)	OKS [23]; patient-rated questionnaire
EQ-5D-5 L	EQ-5D-5 L [23]; patient-rated questionnaire
Knee range of motion	<100 degrees, ≥100 degrees
Return to work	Self-recorded diary
Complication data	Self recorded diary; health system records
Healthcare consumption and related costs	Self recorded diary; health system records

*The primary end-point for data analysis is 6 months post-surgery. All outcome measures will be undertaken pre-surgery, then at 10, 26 and 52 weeks post-surgery, with the exception of return to work and healthcare consumption and related costs, which will not be assessed at baseline.

#### Primary

The primary outcome is walking distance at 6 months post-surgery measured using the 6MWT [24-26]. A functional outcome based on a physical test is a novel choice as a primary outcome in this field given that the convention with most TKA rehabilitation studies is to focus on patient-reported outcomes [16,25-28]. The decision to employ measured mobility as the primary outcome was based on multiple factors. First, functional mobility is a composite of several factors targeted in rehabilitation programs after TKA such as lower limb strength, knee range of motion, and balance [25,26,28-30]. Second, a functional outcome is more likely to be directly influenced by the intervention (rehabilitation), and the intervention aims to improve walking. Third, the 6MWT is highly reproducible within the individual [31]. Fourth, it is likely to be less susceptible to misinterpretation and less culturally sensitive than patient-reported outcomes. Fifth, the test does not appear to suffer from the floor or ceiling effects associated with many patient-reported outcomes [21]. Sixth, an observer-measured outcome is less likely to be influenced by a preference effect compared to a patient-reported outcome, and this is particularly important when the intervention under examination cannot be blinded from the recipient. Together, these attributes mean the results for our primary outcome should be readily translatable to any TKA cohort.

#### Secondary

Secondary outcomes comprise both patient-reported and observer-measured outcomes including a knee pain and function survey (the Knee injury and Osteoarthritis Outcome Score (KOOS) [22], knee range of motion (ROM) (<100 degrees, ≥100 degrees) [32,33], health-related quality of life (the EQ-5D) [34] and the proportion achieving a gait speed of 1.2 m/s during a 15 m walk test). Direct healthcare costs will also be captured using diarized recordings and face-to-face interviews [12,13,15]. Costs recorded will include visits to health professionals, pathology tests, imaging, cost of transport and cost of medication. Indirect costs including time lost from work for the patient or carer will also be explored in a secondary analysis. The extent to which a cost analysis is undertaken will depend on the availability of funds to perform a comprehensive health economic analysis.

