The original plan for the primary outcome was gait speed (m/s) at 6 months post-surgery, with an initial sample size powered to detect an absolute difference of 20% in the proportion of participants at 6 months who achieve the minimum gait speed considered necessary to cross safely at a pedestrian crossing (that is, 1.2 m/s). In the absence of other context-specific data, the data used for this calculation was based on the proportion of TKA participants (37%) who achieved this average gait speed at 6 months post-surgery during a 6MWT having participated in outpatient-based rehabilitation only [18]. This calculation assumed that average gait speed during a 6MWT was representative of the average speed a TKA recipient would achieve during a shorter test, such as crossing a 4- to 6-lane road (approximately 15 m). Aware that the assumption may be overly optimistic, we planned to review - whilst blind to treatment allocation - the proportion in each group achieving an average gait speed of 1.2 m/s during the 15 m walk test after the first 15 randomized participants reached the 10-week follow-up. On review, approximately 70% in each group achieved the requisite gait speed; hence, to expect inpatient rehabilitation to secure this gait speed for over 90% of the participants was deemed unrealistic. The primary outcome remained based around the 6MWT as originally planned, but was converted to the distance walked during this same test. To complement the revised primary outcome, and in the absence of data describing the minimum clinically important difference for the 6MWT, we included a sub-study to evaluate the minimum clinically important difference for measured mobility in this population.

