#### Analyses subsets

Data analysis will be completed using the principle of intention-to-treat [36]. We will include all randomized participants regardless of level of compliance with the protocol. The primary outcome variable is distance measured using the outcome of a 6MWT at 26 weeks.

Analysis of covariance will be used for this primary outcome, with treatment group as the main study factor and walking distance at baseline, weight, BMI, co-morbidities and patient preference as covariates. For participants with a missing outcome measure at 26 weeks, an imputation method will be used [37,38].

The secondary outcome variables include the 6MWT at 10 and 52 weeks post-surgery, the 15 m walk test, EQ5D, Oxford Knee Score, KOOS and knee ROM at most post-surgery time points.

Mixed model analyses will be used for the continuous variables measured repeatedly at 10, 26 and 52 weeks to estimate the treatment group by time effects. These analyses incorporate the missing data that may occur at the follow-up occasions. Baseline measurements of the outcome variables, together with factors such as weight, BMI, co-morbidities and patient preference, will be included as covariates [39]. For the binary outcome measured at 10, 26 and 52 weeks (knee flexion ≥100 degrees or ≤100 degrees), a Generalized Estimating Equation model will be used to test the treatment effect, with the adjustment of the covariates as above.

For the analyses involving the observational arm, the change score in the primary outcome will be compared between the observational group and those in the randomized home group adjusting for other covariates. A lack of significant difference in scores between the two groups will suggest there is no strong preference effect in this trial and we may not need to include preference as a covariate in the RCT analyses. To be consistent with the two RCT groups, we will aim for a minimum 64 participants in the observational group.

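### Knee range is analysed only as pass/fail at 100 degrees, with categories that overlap in one section, and the sections disagree on whether gait speed is a proportion or a measured speed

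*Protocol article*

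**What the plan says.** **Knee range.** Table 2 of the protocol article gives the outcome as two exclusive categories, "<100 degrees, ≥100 degrees", and the Secondary paragraph under Outcome measures repeats them. The section Analyses subsets turns to the model and writes: "For the binary outcome measured at 10, 26 and 52 weeks (knee flexion ≥100 degrees or ≤100 degrees". It continues that "a Generalized Estimating Equation model will be used to test the treatment effect". No section plans an analysis of degrees.

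**Gait speed.** The Secondary paragraph makes the outcome "the proportion achieving a gait speed of 1.2 m/s during a 15 m walk test". Table 2 gives only "15 m walk test; physical test". Analyses subsets also gives no cut-off: "The secondary outcome variables include the 6MWT at 10 and 52 weeks post-surgery, the 15 m walk test". The same section says "Mixed model analyses will be used for the continuous variables measured repeatedly at 10, 26 and 52 weeks", and the only outcome it calls binary is knee flexion.

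**History of the cut-off.** The Sample size section explains that 1.2 m/s was once the basis of the primary outcome. At a review blind to allocation, when the first 15 randomized participants had reached 10 weeks, "approximately 70% in each group achieved the requisite gait speed". The authors judged it unrealistic to expect more than 90% on inpatient rehabilitation, and changed the primary outcome to distance walked in the 6MWT.

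**The concern.** There are three connected problems, all in secondary outcomes.

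1. Knee range is measured in degrees but enters the analysis only as above or below one cut. That discards information for no stated analytic gain.
2. The categories in Analyses subsets both contain exactly 100 degrees, which contradicts the other two places. The label also moves from range of motion to knee flexion.
3. Gait speed is two different endpoints depending on the section: a proportion at a threshold, or a measured speed. Anyone following the Secondary paragraph uses the cut-off that was given up for the primary outcome. Anyone following Analyses subsets uses the mixed model. Unless this is settled beforehand, the choice could be made with the data in view.

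At stake is the precision of two observer-measured secondary outcomes. In an unblinded trial, the section on the primary outcome values observer-measured outcomes as less open to preference effects.

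**Working it through.** **Inputs from the protocol article.** Sample size: 70 per group, 80% power, 5% significance, 400 m versus 460 m, SD 120 m, drop-out below 10%; about 70% reaching 1.2 m/s at 10 weeks. Randomization: 1:1.

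**Assumptions, not in the document.** Two-sided test; roughly normal outcome; a true shift of 0.5 SD, which is the protocol's criterion for the 6MWT and is borrowed here; one visit, no covariates.

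**Step 1: the plan's own figure.** n per arm = 2(1.96 + 0.8416)² × (120/60)² = 2 × 7.849 × 4 = 62.8, so 63. With 10% drop-out, 63/0.9 = 70. The stated sample size reproduces. (A t-test version needs 64 evaluable per arm.)

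**Step 2: information kept after one cut.** If a share p passes, the efficiency relative to the continuous measure is φ(z_p)²/[p(1−p)].
- p = 0.50: 0.3989²/0.25 = 0.637, a loss of 36%. This is the best case over all cuts.
- p = 0.70: z = 0.5244, φ = 0.3477, and 0.3477²/0.21 = 0.576, a loss of 42%.

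**Step 3: power for a 0.5 SD shift, 63 per arm.** The pass rate in the better arm is p₂ = Φ(z_p + 0.5). Power = Φ[(d − 1.96·SE₀)/SE₁], where d = p₂ − p, SE₀ is the pooled and SE₁ the unpooled standard error.

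| Analysis | Pass rates | Power | n per arm for 80% |
|---|---|---|---|
| Continuous | – | 80% | 63 |
| Cut, 50% pass | 50.0% vs 69.1% | 59% | 102 |
| Cut, 70% pass | 70.0% vs 84.7% | 51% | 126 |

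For the 70% row: d = 0.147, SE₀ = 0.0746, SE₁ = 0.0734, and power = 0.506. With 64 per arm, or a slightly different variance formula, it is up to 52%.

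**Step 4: what the 1.2 m/s proportion could detect.** With 63 per arm, 70% versus 90% has 81% power, 70% versus 85% has 52%, and 70% versus 80% has 25%. So 80% power needs about the contrast that the Sample size section calls unrealistic.

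**Step 5: how firm the 70% is.** Read as 10 of 15, the exact 95% interval is 38% to 88%; as 11 of 15, 45% to 92%. It is a 10-week figure, and the share at 26 weeks is not given. No pass rate at 100 degrees appears anywhere, so for knee range only the minimum loss of 36% can be stated.

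**Step 6: definitions side by side.**

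| Section | Gait speed | Knee range |
|---|---|---|
| Table 2 | no cut-off | exclusive at 100 |
| Secondary | proportion at 1.2 m/s | exclusive at 100 |
| Analyses subsets | no cut-off; not named as binary | 100 in both categories; GEE |

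**The case against.** The strongest reply is that, for gait speed, the analysis section read as written already does what is asked: no cut-off is given, knee flexion is the only binary outcome, and continuous variables go to the mixed model. This stands. A reader might infer that gait speed is definitely reduced to pass/fail; the documents show a conflict between sections, not a settled choice.

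A reader might also infer that the cuts lie near a ceiling and make a null result likely. The documents do not support that. Seventy percent is not close to a ceiling, it comes from about 15 participants, and nothing is reported for 100 degrees. At 70%, power for a 0.5 SD shift is about even odds. That shift is itself borrowed from the 6MWT, and the planned models use covariates and repeated visits, so the power figures compare two analyses and do not forecast results.

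Nor are these the only observer-measured secondary outcomes. The 6MWT at 10 and 52 weeks is also secondary, continuous and assessed blind, so walking is measured without a cut-off at every follow-up.

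Dropping 1.2 m/s as the primary basis was a sample-size decision. Keeping a threshold tied to safe road crossing as a secondary summary is compatible with it. The model for a secondary proportion can also be left to an analysis plan not shown here, so the absence of one is no fault in itself. One could object that GEE makes a stricter missing-data assumption than the mixed model. That is minor with drop-out planned below 10%, and no reason to avoid GEE for a supportive analysis.

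What remains is the binary-only analysis of knee range, the overlap at 100 degrees, and the conflicting definitions of gait speed.

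**Conclusion.** The point holds as a secondary-outcome matter. Knee range loses information under every definition given: at least 36% if flexion is roughly normal, more if the cut lies away from the median. Gait speed suffers a similar loss, 42% at a 70% pass rate, only if the Secondary paragraph governs; if Table 2 and Analyses subsets govern, nothing is lost. In power terms, 80% for a continuous analysis becomes about 59% at a 50% pass rate and 51% to 52% at 70%, assuming normality, a 0.5 SD shift and 63 to 64 evaluable per arm. The overlap at 100 degrees and the disagreement over gait speed are errors of wording whatever those assumptions. The primary 6MWT analysis, its sample size and the 6MWT at 10 and 52 weeks are unaffected.

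**What to change.** State in the Secondary paragraph, Table 2 and Analyses subsets alike that 15 m gait speed (m/s) and knee flexion (degrees) are continuous outcomes, analysed in the mixed model already planned for 10, 26 and 52 weeks. Keep the proportions reaching 1.2 m/s and 100 degrees as supportive analyses, both by GEE. Use below 100 versus 100 or more everywhere, and one name for the knee measure.

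The cost is wording, plus one numeric field on the form if flexion is now logged only as a category. The downside is that the threshold proportions, which have a direct practical meaning, are no longer the lead summaries; they are still reported.

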### Baseline and other data

Demographic data (age, gender, height, weight, body mass index (BMI), level of education, co-morbidities) will be collected at baseline, and complication data (such as presentation to emergency department, re-admission, re-operation, knee manipulation, wound infection, venous thrombo-embolism and death) will be collected until 12 months post-surgery. Preference for rehabilitation mode (home-based rehabilitation program, inpatient rehabilitation program or either) will be ascertained prior to surgery and after formal rehabilitation has ceased [35].

### Follow-up

A summary of the follow-up schedule is shown in Figure 1. Researchers will perform assessments at baseline, 10 weeks, 6 months and 1 year. The co-ordinating investigator will call each participant within the week preceding each of their follow-up appointments to promote participant retention and completion of follow-up.

### Sample size

The primary end-point in this trial is functional mobility at 6 months post-surgery measured using the distance walked during a 6MWT. Seventy participants in each group (140 in total) will provide 80% power at a significance level of 5% to detect an increase in walking capacity from 400 m to 460 m between the HO and HI groups, respectively, in the 6MWT at 6 months post-surgery, assuming a SD of 120 m and a drop-out rate of <10%. The SD of 120 is a conservative estimate of the SD of the mean 6MWT at 6 months [18,25]. Using a 0.5SD criterion, this sample will be powered to detect a moderate effect size of 60 m difference in walking distance. If the actual SD of the sample collected is smaller than the assumed value, say 100 instead of 120, the study will remain powered to detect a moderate effect size of 0.5SD.

The original plan for the primary outcome was gait speed (m/s) at 6 months post-surgery, with an initial sample size powered to detect an absolute difference of 20% in the proportion of participants at 6 months who achieve the minimum gait speed considered necessary to cross safely at a pedestrian crossing (that is, 1.2 m/s). In the absence of other context-specific data, the data used for this calculation was based on the proportion of TKA participants (37%) who achieved this average gait speed at 6 months post-surgery during a 6MWT having participated in outpatient-based rehabilitation only [18]. This calculation assumed that average gait speed during a 6MWT was representative of the average speed a TKA recipient would achieve during a shorter test, such as crossing a 4- to 6-lane road (approximately 15 m). Aware that the assumption may be overly optimistic, we planned to review - whilst blind to treatment allocation - the proportion in each group achieving an average gait speed of 1.2 m/s during the 15 m walk test after the first 15 randomized participants reached the 10-week follow-up. On review, approximately 70% in each group achieved the requisite gait speed; hence, to expect inpatient rehabilitation to secure this gait speed for over 90% of the participants was deemed unrealistic. The primary outcome remained based around the 6MWT as originally planned, but was converted to the distance walked during this same test. To complement the revised primary outcome, and in the absence of data describing the minimum clinically important difference for the 6MWT, we included a sub-study to evaluate the minimum clinically important difference for measured mobility in this population.

### Data management and analysis

#### Data management

Data will be sent by blinded assessors to blinded data entry staff for collation and data entry, with range checks for data values. All databases will be password protected and stored in secure areas.

#### Descriptive analyses at baseline

Comparability of intervention groups will be investigated at baseline. Descriptive statistics will be presented, including summary statistics of potential confounding variables.

#### Analyses subsets

Data analysis will be completed using the principle of intention-to-treat [36]. We will include all randomized participants regardless of level of compliance with the protocol. The primary outcome variable is distance measured using the outcome of a 6MWT at 26 weeks.

Analysis of covariance will be used for this primary outcome, with treatment group as the main study factor and walking distance at baseline, weight, BMI, co-morbidities and patient preference as covariates. For participants with a missing outcome measure at 26 weeks, an imputation method will be used [37,38].

The secondary outcome variables include the 6MWT at 10 and 52 weeks post-surgery, the 15 m walk test, EQ5D, Oxford Knee Score, KOOS and knee ROM at most post-surgery time points.

Mixed model analyses will be used for the continuous variables measured repeatedly at 10, 26 and 52 weeks to estimate the treatment group by time effects. These analyses incorporate the missing data that may occur at the follow-up occasions. Baseline measurements of the outcome variables, together with factors such as weight, BMI, co-morbidities and patient preference, will be included as covariates [39]. For the binary outcome measured at 10, 26 and 52 weeks (knee flexion ≥100 degrees or ≤100 degrees), a Generalized Estimating Equation model will be used to test the treatment effect, with the adjustment of the covariates as above.

For the analyses involving the observational arm, the change score in the primary outcome will be compared between the observational group and those in the randomized home group adjusting for other covariates. A lack of significant difference in scores between the two groups will suggest there is no strong preference effect in this trial and we may not need to include preference as a covariate in the RCT analyses. To be consistent with the two RCT groups, we will aim for a minimum 64 participants in the observational group.

For the sensitivity analysis, the above analysis used for the primary and secondary outcome variables will be performed ‘as-treated’, analyzing patients according to the treatment they actually received and excluding those with missing outcome measures. It will only include patients who were compliant with the intervention protocol. Compliance for the HI group will be defined as attendance of a minimum of 7 days of inpatient rehabilitation, along with attendance at no less than two outpatient sessions. Compliance for the HO group will be defined as attendance at no less than two outpatient sessions. There will be procedures put in place to minimize loss to follow-up, such as obtaining multiple contact details at time of consent and reminders that assessments are due. The age, gender and height of participants will be used as stratification variables in the randomization procedure via a minimization algorithm. The mixed model analysis indicated above will include these three variables as additional covariates to incorporate the possible within-treatment group correlation associated with stratification [39].

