### Randomization and allocation concealment

Randomization will take place following surgery once it has been confirmed that participants are likely to be cleared for discharge home by post-operative day 5. If it is determined that there is a need for rehabilitation at this time - owing to a post-operative complication - such patients will not be eligible to participate in the study.

A centralized randomization service will be used for participant randomization using a 1:1 ratio, providing secure, coded randomization via telephone. Group allocation, therefore, will be concealed from all parties until the result of the randomization is known. Participants will be randomized to one of the two intervention groups using the method of minimization stratified for variables that affect the primary outcome (distance walked in the 6MWT), age (≤68 years, >68 years), height (≤163 cm, >163 cm), and gender [19].

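### The primary ANCOVA omits age and gender, and height by name, although allocation is minimised on all three and the mixed model adjusts for them; the cost is a somewhat conservative test

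*Protocol article*

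**What the plan says.** Three statements in the protocol article bear on this point.

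- *Randomization and allocation concealment*: participants are allocated 1:1 "using the method of minimization stratified for variables that affect the primary outcome". The factors are age (cut at 68 years), height (cut at 163 cm) and gender.
- *Analyses subsets*, primary outcome: ANCOVA of the 26-week walking distance, "with treatment group as the main study factor and walking distance at baseline, weight, BMI, co-morbidities and patient preference as covariates". Missing 26-week values are to be imputed by a method that is cited but not described.
- *Analyses subsets*, last paragraph: "The mixed model analysis indicated above will include these three variables as additional covariates". The reason given is the correlation within treatment groups that stratification may induce.

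The Abstract (Methods/Design) also says that baseline differences in potential confounders will be accounted for where required. That is conditional on differences being seen. Minimisation is meant to prevent such differences on these three factors, so this sentence does not put them into the primary model.

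**The concern.** The protocol recognises that an analysis should reflect the factors used to balance allocation. It applies this to the repeated-measures model but not to the test that decides the trial. The stated reason for adjusting the mixed model applies equally to the ANCOVA.

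The mechanism is standard. Balancing on prognostic factors removes their contribution to the chance difference between arms. A model that leaves them out still counts their variance as residual noise. The reported standard error then exceeds the true one, the confidence interval is wider than it need be, and the test rejects less often than its nominal 5%. *Significance* says the trial will either support or refute the need for inpatient rehabilitation, so a needlessly wide interval matters most if the result is non-significant.

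**Working it through.** **Inputs from the article (*Sample size*).** 70 per group, 80% power, 5% significance, 400 m against 460 m (60 m), SD 120 m, drop-out below 10%. Sidedness is not stated; two-sided is assumed. A one-sided test would need only 50 per arm.

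**Inputs not in the article (assumed).**
- r: the share of residual variance that age, height and gender explain beyond the listed ANCOVA covariates. Range 0.05 to 0.20.
- B: the share of variance that the listed covariates explain. Either 0, or 0.36 (baseline correlation 0.6, since 0.6² = 0.36).

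**Step 1: the plan's own figure.** n per arm = 2 × (1.96 + 0.8416)² × 120² / 60² = 62.8, so 63. With 10% drop-out, 63 / 0.90 = 70 per arm, 140 in total. The stated sample size reproduces; power with 63 per arm is 80.1%. This calculation uses the unadjusted SD and takes no credit for any covariate.

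**Step 2: standard errors with 63 completers per arm.**
- Reported, factors omitted: SE_rep = 120 × √(1 − B) × √(2/63). This is 21.38 m at B = 0 and 17.10 m at B = 0.36.
- True, factors balanced: SE_true = SE_rep × √(1 − r).
- Inflation: SE_rep / SE_true = 1/√(1 − r).

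**Step 3: type I error and power at 60 m.**
- Actual type I error, factors omitted: 2 × Φ(−1.96 / √(1 − r)).
- Power, factors omitted: Φ((60 − 1.96 × SE_rep) / SE_true).
- Power, factors included: Φ(60 / SE_true − 1.96).

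| r | SE too large by | Actual type I error | Power at B = 0: omitted / included | Power at B = 0.36: omitted / included |
|---|---|---|---|---|
| 0.05 | 2.6% | 4.4% | 80.7% / 82.1% | 94.4% / 94.9% |
| 0.10 | 5.4% | 3.9% | 81.4% / 84.1% | 94.9% / 95.9% |
| 0.20 | 11.8% | 2.8% | 82.8% / 88.0% | 95.8% / 97.5% |

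At r = 0 nothing is lost.

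**Step 4: check by simulation.** The formulas assume exact balance. Minimisation was simulated on three dichotomised factors with 126 completers and 3,000 runs per setting. The assignment probability of 0.8 is an assumption.
- r = 0.20, B = 0: mean reported SE 21.4 m against an empirical 19.4 to 19.6 m. Null rejection was 3.0% without the factors and 4.2% with them; power was 79.4% against 86.2%.
- r = 0.10, B = 0: power 79.5% against 83.2%.
- r = 0.20, B = 0.30: power 92.8% against 95.9%.

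The direction agrees. The simulated power gaps are a little wider than the formulas give (6.8 against 5.2 points at r = 0.20, B = 0).

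**Step 5: is height really missing?** BMI is weight divided by height squared, so weight and BMI together determine height exactly. Entered linearly, they explain about 97% to 98% of its variance under assumed distributions (BMI mean 32, SD 4 to 6; height centred near 163 cm; gap between sexes 11 to 15 cm). Under the same assumptions they explain about 40% to 56% of the variance in gender. Neither stands in for age.

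**The case against.** The strongest reply is that the loss is small and falls on the safe side. The estimate is unbiased and false-positive risk is not raised. Baseline walking distance is already in the model; if age, height and gender affect walking distance, baseline should carry part of their effect. Weight and BMI carry nearly all of height and, through it, part of gender. The larger values of r therefore have no support in the article, and with a predictive baseline the power forgone at the planned effect is 2 points or less.

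Most of this stands, and it sets the size of the point. It does not remove the inconsistency: the protocol gives a reason to adjust and then does not apply it to its primary test.

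Three stronger readings are tempting and are not supported.

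- A reader might infer that adding the factors lifts power from 80% to between 84% and 91%. Gains of that order arise at r = 0.10 to 0.30 only if the true effect is set at about 48 m with a baseline correlation of 0.6. The article plans "to detect an increase in walking capacity from 400 m to 460 m between the HO and HI groups", which is 60 m, and at that effect the gain is as tabulated.
- A reader might infer that the trial is underpowered. The 140 rests on the unadjusted SD, so analytic power stays at or above 80% even with the factors omitted.
- A reader might infer that the ANCOVA and the mixed model are rival primary analyses. *Analyses subsets* assigns the 26-week walking distance to the ANCOVA and lists only the 10- and 52-week distances as secondary, so the deciding analysis is identified.

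**Conclusion.** The point holds as a minor to moderate one. The primary ANCOVA should adjust for the factors on which allocation is minimised, as the mixed model does; age and gender are the clear gaps, and height is mostly covered.

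At an assumed r of 0.05 to 0.20, the reported standard error is about 3% to 12% too large and the actual type I error about 4.4% to 2.8%. At the planned 60 m and SD 120 m, the power forgone is about 1 to 5 points if the other covariates explain nothing (up to about 7 in simulation), and about 0.5 to 2 points if baseline distance correlates at about 0.6. The loss is relative to the adjusted analysis, not to the planned 80%.

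The inconsistency in the text is certain. Its size is not: r, B and the assignment probability are all assumptions.

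**What to change.** Extend the sentence that adds the three minimisation factors so that it covers the primary 26-week ANCOVA as well as the mixed model. In practice, add age and gender, and keep only two of weight, height and BMI, because the third is determined by the other two and entering all three makes the model nearly collinear. Use the same covariates in the model that imputes missing 26-week values.

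The cost is two degrees of freedom (three if height were entered as well), with about 126 completers. No new data are needed: age, height and gender are recorded at baseline and used for randomisation. Recruitment was still active when the article was submitted and the analysts are blinded to allocation, so on the article's own account the change could be fixed before any result was known. The sample size needs no change.
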